### Ethical Considerations

A waiver of written consent was granted by the University of Texas Health Science Center at Houston (UTHealth Houston) Institutional Review Board based on a category III exemption and Title 45 of the Code of Federal Regulations part 46 as the intervention does not pose more than minimal risk to patients or caregivers [12]. The informative video can be considered a “benign behavioral intervention that is brief in duration, harmless, painless, not physically invasive, not likely to have a significant adverse lasting impact on the subjects, and there is no reason to think the subjects will find the interventions offensive or embarrassing” [13]. Additionally, there is no standard of care regarding optimal patient decisional counseling, and this intervention is a reasonable strategy for usual care. Therefore, we will obtain verbal consent for enrollment, and patients will receive a letter of intent prior to survey completion.

The institutional review board of McGovern Medical School at UTHealth Houston approved the study protocol on January 21, 2025. Enrollment began on March 17, 2025, and is scheduled to continue for 18 months. Information and data from patients included in the study will be accessed only by designated study personnel, and the data will be collected in a secure database and deidentified. The ADVISE (Advancing Discussions Using a Video-Based Support Tool About End-of-Life Care) project (NCT06804226) was registered on January 31, 2025, on ClinicalTrials.gov.

### Randomization and Blinding

This is a single-center pilot randomized trial. Randomization will be performed in a 1:1 ratio between the intervention and usual care groups using REDCap (Research Electronic Data Capture; Vanderbilt University). We plan to stratify based on whether the patient or a surrogate decision-maker watches the video aid. Allocation will be performed using the REDCap randomization module, after which a research assistant will administer the video intervention. Thus, providers will be blinded to treatment group. The project statistician will be blinded to group assignment.

### Sample Size Calculation

We plan to conduct the largest feasible randomized controlled trial (RCT) with enrollment lasting 18 months. We conservatively estimate that at least 15 patients will be enrolled per month, with the potential for 270 randomized patients during the study period. A Bayesian analysis will be performed to estimate the probability of treatment benefit. This estimate is based on recommendations for pilot trials with limited sample size and power in frequentist analyses to identify conclusive treatment effects [14].

### Data Analysis Plan

Analysis will be performed on a per-patient basis. For patients who are incapacitated and unable to consent for themselves, their surrogate decision-makers will serve as the participant for analysis. The number of screened patients and reasons for exclusion will be reported. Protocol violations and reasons for those violations will be reported and detailed. All analyses will be based on the intention-to-treat principle. Regarding the primary end point, we will estimate the risk ratio between the intervention and usual care groups together with a 95% Wald CI. For other outcome variables, we will implement 2-group comparisons using the Wald test for dichotomous variables and the Wilcoxon rank-sum test for continuous variables. ICU-free days and ventilator-free days refer to the number of days during admission without intensive care or a ventilator [15]. In case of a death event, these variables are set to a value of 0. The principal investigator will audit data collection to ensure that the data are accurate, consistent, complete, and reliable.

For the primary end point, in addition to the frequentist inference, we will conduct a Bayesian analysis to enhance the knowledge gained from the study. Bayesian analysis enhances the clinical decision-making process by integrating existing evidence with data from a new study to estimate the probability of an outcome of interest. In contrast, frequentist analysis assesses the likelihood of observing the obtained results or more extreme outcomes. For each group, we will use the conjugate β prior for the probability of transition in code status. The parameter values for β distribution will be chosen to center a symmetrical distribution at 0.5, and the corresponding distribution for the risk ratio will be centered at 1 with a credible interval of 0.5 to 2.0, resulting in a neutral prior [16]. Additionally, we will perform sensitivity analysis by identifying suitable β prior distributions to generate enthusiastic and skeptical priors. We will use the JAGS software (version 4.3.2) for Bayesian analysis. All other statistical analyses will be performed using the SAS software (version 9.4; SAS Institute).

We plan to perform several subgroup analyses, including comparisons based on race, gender, health literacy assessed via the validated Brief Health Literacy Screening Tool, and surrogate decision-maker vs patient watching the video [17]. The Brief Health Literacy Screening Tool has been incorporated into the study and will be administered simultaneously.

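### Randomization is stratified by patient versus surrogate, but the stated primary and secondary analyses do not use the stratum; if transition rates differ by stratum, precision and power are lost

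*Protocol article*

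**What the plan says.** On the design, the Randomization and Blinding section of the protocol article states: "Randomization will be performed in a 1:1 ratio between the intervention and usual care groups using REDCap". It then names a single stratification factor: "We plan to stratify based on whether the patient or a surrogate decision-maker watches the video aid". It does not describe blocks.

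On the analysis, the Data Analysis Plan section says of the primary endpoint that "we will estimate the risk ratio between the intervention and usual care groups together with a 95% Wald CI". The other outcomes get two-group comparisons, by the Wald test if dichotomous and the Wilcoxon rank-sum test if continuous. For the Bayesian analysis of the primary endpoint: "For each group, we will use the conjugate β prior for the probability of transition in code status". No stratum or covariate term is named. The patient/surrogate factor returns only in the list of subgroup analyses that closes that section.

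On size, the Sample Size Calculation section gives an accrual-based figure, "with the potential for 270 randomized patients during the study period". It sets no power target and refers to "recommendations for pilot trials with limited sample size and power in frequentist analyses". The article states no transition rate, no surrogate share and no target effect.

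**The concern.** A factor that was balanced by design should normally be carried into the analysis. When the factor is prognostic, an analysis that leaves it out keeps the between-stratum variation in its variance.

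There is reason to think that this factor is prognostic. According to the Intervention Group section, surrogates act only for patients who lack decision-making capacity. According to Study Population, patients at any level of care are eligible and those with existing limitation orders are excluded. According to Limitations, an active choice of full code is not tracked. A counted transition is therefore essentially a move away from full code, and its rate may well differ between patients who decide for themselves and those who cannot. The article gives no figure for this.

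What is at stake is precision in a trial that already concedes limited frequentist power.

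**Working it through.** **The plan's own figure.** The sample size is accrual times duration: 15 per month × 18 months = 270, which reproduces. At 1:1 that is n = 135 per arm. There is no power calculation to reproduce.

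**Inputs.** From the article: N = 270, 1:1 allocation, one binary stratum, risk ratio (RR) with 95% Wald interval. Assumed, because the article does not give them: the surrogate share w, the control-arm transition rates in patients (p) and surrogates (s), and a common true RR of 1 or 1.5.

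**Formulas.** Let m = (1 − w)p + ws be the overall control rate.

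- Crude analysis: Var(log RR) = 1/(n·m·RR) + 1/(n·m) − 2/n.
- Mantel-Haenszel RR with Greenland-Robins variance, arms equal within each stratum, at expected counts: Var(log RR) = 1/(n·m·RR) + 1/(n·m) − (2/n)(1 + C).
- Here C = w(1 − w)(s − p)²/m², the squared coefficient of variation of the control rate across strata.

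The crude variance is therefore larger by (2/n)·C. This is zero if the two rates are equal and grows with their relative spread.

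**Worked case: w = 25%, p = 5%, s = 30%, RR 1.5.**

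- m = 0.75 × 0.05 + 0.25 × 0.30 = 0.1125.
- C = 0.25 × 0.75 × 0.25² / 0.1125² = 0.926.
- Crude variance = 1/22.78 + 1/15.19 − 2/135 = 0.0949, so SE = 0.308.
- Stratified variance = 0.0949 − (2/135) × 0.926 = 0.0812, so SE = 0.285.
- Ratio = 0.285/0.308 = 0.925, a reduction of about 7%. At RR 1 the same steps give 0.342 and 0.321, a reduction of 6%.

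**Simulation.** It used 270 patients and at least 20,000 trials per scenario, comparing the crude log RR and its Wald interval with the Mantel-Haenszel RR and its Greenland-Robins interval. SE reductions and coverage span RR 1 and 1.5; power is at RR 1.5. The power and crude-coverage columns assume balance within strata.

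| Surrogate share | Control rate, patient / surrogate | Stratified SE smaller by | Power, crude → stratified | Crude coverage |
|---|---|---|---|---|
| 25% | 10% / 10% | 0% | no change | about 96% |
| 25% | 10% / 20% | about 1% | 27.7% → 28.4% | about 96% |
| 25% | 5% / 30% | 6-7% | 23% → 28-29% | about 97% |
| 30% | 5% / 40% | 10-13% | 32% → 45-46% | 97.5-98% |
| 40% | 5% / 50% | 15-19% | 56% → 75% | 98-98.5% |

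Coverage of the stratified interval stays at 95-96%.

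**If allocation within strata is not blocked.** Crude coverage in the last three rows falls to about 95-96%, so the interval is then calibrated. The loss of efficiency remains: power is 24% versus 28%, 34% versus 44%, and 55% versus 75%.

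**Secondary outcomes and the Bayesian model.** These were set against the design by reading only. One conjugate beta per arm has no parameter for the stratum, and the Wilcoxon rank-sum test is the unstratified test. No stratified posterior was computed.

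**The case against.** The strongest reply is that the article nowhere calls the risk ratio crude or unadjusted. Mantel-Haenszel and modified Poisson intervals are Wald intervals too, and a condensed article can leave stratum terms to an analysis plan that is not shown. This stands in part: for the risk ratio the gap is an omission that such a plan could fill. It does not cover the other methods. A conjugate beta per arm and a rank-sum test are named choices, and a plan that added the stratum would have to replace them. The Bayesian model is also the analysis that the Sample Size Calculation section leans on.

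A second reply is that the benefit is hypothetical. That also stands as a limit. Nothing in the article shows that surrogates transition more often, and at 10% versus 20% the gain is about one point of power or less.

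A reader might go further and infer that the planned intervals are certainly too wide and the test certainly conservative. The article does not support this. Over-coverage needs both a prognostic stratum and balance within strata, and no block structure is described. A reader might also apply the frequentist percentages to the posterior. They do not transfer. The neutral prior (centred at 0.5, RR interval 0.5 to 2.0) amounts to roughly Beta(9,9) per arm. In the 25%, 5%/30% case at RR 1.5 it gives a posterior SD of log RR of about 0.25, against 0.31 for the crude and 0.29 for the Mantel-Haenszel estimate, so the prior largely sets the width there.

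**Conclusion.** The point holds as a conditional one. The design uses the patient/surrogate stratum, the stated analysis does not, and two of the named methods cannot. Any cost falls on precision and power. The error is in the conservative direction, so the validity of the trial's conclusion is not in question.

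The size depends on rates and a surrogate share that the article does not report. It runs from nothing (equal rates) to an SE 15-19% smaller and about 19 points of power (5% versus 50%, 40% surrogates). There is no stated power to fall short of, so the loss is relative to a stratified analysis of the same data. This is an improvement worth making, not a flaw that must be repaired for the result to stand.

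**What to change.** Make these changes before unblinding. The Results section reports 270 patients enrolled as of April 2026 and an abstract planned by July 2026. The project statistician is blinded, so the change can still be prespecified.

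- **Primary risk ratio:** stratify by, or adjust for, the randomization stratum, using Mantel-Haenszel with the Greenland-Robins interval or modified Poisson regression with robust SE. Keep the crude RR as supportive.
- **Bayesian model:** use stratum-specific transition rates by arm in JAGS and report a risk ratio standardized over the strata. Re-specify the neutral, enthusiastic and skeptical priors to match. A common log RR need not be imposed, since the same strata are to be compared as subgroups.
- **Secondary outcomes:** use stratified tests, such as van Elteren in place of the rank-sum test.
- **If the unadjusted analysis is kept:** say so and give the reason.

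The cost is wording, standard code and a modest re-specification of the priors. No new data are needed. If the stratum proves weakly prognostic, almost nothing is gained, but almost nothing is lost.

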**Methods:**

This is a single-center randomized controlled trial evaluating the use of a video conversation aid to facilitate discussions of code status. The video intervention will be compared to usual care in the largest feasible pilot randomized controlled trial with the goal of estimating its benefit for patient-centered outcomes. All trauma patients aged 65 years and older admitted following injury are eligible. Incarcerated people, patients with existing do-not-resuscitate or do-not-intubate orders, patients admitted while in hospice care, and patients not expected to survive over 24 to 48 hours will be excluded. The primary outcome is transitions in code status. Secondary outcomes will include perceived success of CPR, video acceptability and effectiveness, knowledge of life-sustaining care outcomes and complications following CPR, participant desire for more information regarding life-sustaining care, hospital-free days, intensive care unit–free days, ventilator-free days, discharge disposition, decisional conflict score, and rate of interventional procedures (eg, tracheostomy, feeding tube placement, and dialysis initiation).

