### Procedures and Outcomes

A research assistant will administer a survey to each participant at discharge either collected verbally or completed electronically via QuestionPro. Patients’ decision-making capacity is determined by the primary clinical team. For patients who die during admission, surrogate decision-makers will be contacted after discharge. Demographics, injury characteristics, length of stay, preexisting advanced directives, and disposition will be collected using the institutional trauma registry. Each participant will be assigned a study-specific number.

The primary outcome will be the rate of transition in code status. Prior institutional data have shown that a minority of patients have advanced directives or code status discussions with their providers; therefore, this serves as a proxy for increased patient or surrogate decision-maker knowledge.

Secondary outcomes will include perceived success of CPR, knowledge of life-sustaining care outcomes and complications following CPR, and participant desire for more information regarding life-sustaining care. These will all be assessed using a Likert scale via a survey at the time of discharge. Decisional conflict score will also be assessed at the time of discharge using an electronic survey. Hospital-free days, intensive care unit (ICU)–free days, ventilator-free days, discharge disposition, and rate of interventional procedures (eg, tracheostomy, feeding tube placement, and dialysis initiation) will be collected from the electronic medical record.

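### Secondary outcomes are assigned tests without a named effect measure or interval, which suits the trial's estimation goal poorly, chiefly for the rank-sum outcomes

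*Protocol article*

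**What the plan says.** The abstract (Methods) describes a comparison of the video with usual care "in the largest feasible pilot randomized controlled trial with the goal of estimating its benefit for patient-centered outcomes". The Sample Size Calculation section gives a feasibility count of 270 and rests its Bayesian approach on "recommendations for pilot trials with limited sample size and power in frequentist analyses to identify conclusive treatment effects".

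Under Procedures and Outcomes, "The primary outcome will be the rate of transition in code status". The Data Analysis Plan says of this end point that "we will estimate the risk ratio between the intervention and usual care groups together with a 95% Wald CI", and then: "For the primary end point, in addition to the frequentist inference, we will conduct a Bayesian analysis".

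The remaining outcomes get one sentence: "For other outcome variables, we will implement 2-group comparisons using the Wald test for dichotomous variables and the Wilcoxon rank-sum test for continuous variables". They include the decisional conflict score, the Likert survey items (perceived CPR success, knowledge, wish for more information), hospital-, ICU- and ventilator-free days, and procedure rates. No effect measure or interval is attached to any of them.

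The Randomization and Blinding section plans stratification by whether the patient or a surrogate watches the video. The sentence on the other outcomes does not mention that factor. The factor reappears only as a planned subgroup.

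**The concern.** Adjacent sentences give the primary end point an estimate and the other outcomes a test. A trial that aims to estimate benefit on several outcomes, and concedes limited frequentist power, gains little from naming significance tests for all but one of them.

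The affected outcomes are not peripheral. The Introduction and Discussion hypothesize better knowledge of life-sustaining care, and Procedures and Outcomes presents code status transition as a proxy for knowledge. The proxy thus has a risk ratio, an interval and a Bayesian analysis, while the survey measure of knowledge has only a named test.

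At stake is how null results are read. At this size a non-significant p-value does not separate the absence of an effect from a missed effect of useful size. An interval shows which effects remain plausible.

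**Working it through.** **Sample size.** The plan's own figure reproduces: 15 patients per month × 18 months = 270. With 1:1 allocation (Randomization and Blinding) that is 270 / 2 = 135 per arm. The Results section reports 270 enrolled as of April 2026. This is a feasibility count. The article states no power, SD, event rate or target effect, so there is no power figure to reproduce.

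**Assumptions for what follows.** 135 analyzed per arm, complete survey response, two-sided 5% level, normal approximations. Event rates and SD shifts are assumed because the article gives none.

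**Continuous outcomes.**
- Shift detectable with 80% power, t-test: (1.96 + 0.84) × √(2/135) = 0.34 SD.
- Rank-sum test, with its relative efficiency of 0.955 for normal data: 0.341 / √0.955 = 0.35 SD.
- Power for a comparison of means: about 38% for a 0.2 SD shift and 69% for 0.3 SD.
- 95% CI half-width for a standardized mean difference: 1.96 × √(2/135) = 0.24 SD.
- 95% half-width for the probability of superiority, the effect measure that belongs to the rank-sum test, using its null variance: 1.96 × √(271 / (12 × 135²)) = 0.07.

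**Dichotomous outcomes.** The half-width for a risk difference is 1.96 × √(2p(1−p)/135). For a risk ratio the interval is the estimate multiplied and divided by exp(1.96 × √(2(1−p)/(135p))). The last column is power for a 10-point absolute increase from rate p.

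| Assumed rate p | Risk difference, ± points | Risk ratio, ×/÷ | Power for +10 points |
|---|---|---|---|
| 5% | 5.2 | 2.83 | 79% |
| 10% | 7.2 | 2.05 | 64% |
| 20% | 9.5 | 1.61 | 48% |
| 30% | 10.9 | 1.44 | 41% |
| 50% | 11.9 | 1.27 | 38% |

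**What an interval adds.** Take two non-significant results on a score outcome. An observed difference of 0 SD gives an interval of −0.24 to 0.24. An observed difference of 0.15 SD gives 0.15 ± 0.24, or −0.09 to 0.39. Both fail the test, but the first excludes a benefit of 0.3 SD and the second does not. The test decision alone reports them alike.

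**Where the gap is real.** A Wald test is an estimate divided by its standard error, so the analysis that yields the test also yields an effect and an interval. For dichotomous outcomes only the choice of scale and the commitment to report are missing. A rank-sum test has no effect size in its usual output: a shift, a probability of superiority or an odds ratio must be chosen, and the article chooses none. I read the Likert items as falling under this test, since the article names methods only for dichotomous and continuous variables. The interpretive problem is plainest for ICU- and ventilator-free days, which are set to 0 at death, because a rank-sum p-value does not express benefit in usable units.

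**The case against.** The strongest reply is that this is a condensed article. Effect measures for secondary outcomes are ordinary SAP content, the SAP is not shown, and naming the primary effect measure and then the secondary tests may be simple compression. Four further points support it:
- The aim of estimating benefit is met where the plan places it, since the primary end point has a risk ratio, an interval and Bayesian analyses under neutral, enthusiastic and skeptical priors.
- The article never lists which outcomes count as patient-centered.
- The remark on power serves to justify the Bayesian analysis and does not address the secondary outcomes.
- The 0.955 factor holds for normal data, not for Likert items or free days with zeros at death.

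Much of this stands. A reader might infer that the trial will publish bare p-values, or that it fails its estimation goal altogether. The document supports neither: it does not rule out estimates, the primary has one, and a Wald test contains one. The lack of a stated adjustment for the stratification factor may also be condensation. The figures in SD units are illustrations.

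What does not fall away is the stated choice of method. The article did not leave secondary analysis to another document. It named the methods, and it drew the line between estimation and testing itself. For the rank-sum outcomes the named method produces no effect size, and the stated goal covers outcomes in the plural.

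**Conclusion.** The point holds as a free improvement, not as an error: no stated figure is wrong. For the secondary outcomes the article names two-group tests, with no effect measure, interval or stratification factor, and this fits poorly with its estimation goal and its own remark on power. The mismatch is real for the rank-sum outcomes (decisional conflict, Likert items, free days) and slight for the dichotomous ones.

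Its practical size is the uncertainty that a test decision alone would hide: roughly ±0.24 SD on a score, ±0.07 on the probability of superiority, and ±5 to ±12 percentage points on a risk difference. These rest on 135 analyzed per arm and on assumed rates, and missing surveys would widen them. The conclusion does not depend on the exact values.

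**What to change.** Before unblinded analysis, state one between-group effect with a 95% CI as the reported result for each secondary outcome:
- **Dichotomous outcomes:** a risk ratio or risk difference from the same Wald model that supplies the test.
- **Likert items and free days:** a probability of superiority or a proportional-odds odds ratio.
- **Decisional conflict score:** a Hodges-Lehmann shift or a probability of superiority.

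Stratify by, or adjust for, the patient/surrogate randomization factor. Keep the p-values as supplementary. Any of these measures would do; what matters is fixing one per outcome in advance.

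The cost is a few sentences in the analysis plan and some lines of code, with no new data. Timing matters more than effort: the Results section reports 270 enrolled as of April 2026 and plans an abstract by July 2026, so the measures should be fixed while the project statistician is still blinded. If the SAP already names them, a cross-reference is enough.

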This multidisciplinary, collaborative research project will evaluate the effectiveness of a video aid to improve communication and patient-centered outcomes in older injured adults. This video conversation aid is not intended to replace code status discussions between patients and health care providers but to promote these discussions. The goal is to overcome identified barriers to adequate code status discussions by providing a clear message with no medical jargon; supplying accurate prognostic information; and, ultimately, enhancing informed consent so that patients can ensure that their care choices align with their preferences. We hypothesize that our video aid will increase the rate of code status transitions, with more patients documenting their code status. Additionally, we hypothesize that our video aid will improve knowledge of life-sustaining care and increase code status discussions.

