### Study Population

All English- or Spanish-speaking patients aged 65 years or older admitted to any level of care following traumatic injury will be screened for study eligibility. As this is a pilot trial, we will have minimal exclusion criteria except for (1) incarcerated people, (2) existing do-not-resuscitate (DNR) or do-not-intubate (DNI) orders, (3) patients admitted while in hospice care, and (4) patients not expected to survive over 24 to 48 hours. Incarcerated individuals are excluded due to being a vulnerable population in a study that waives informed consent. Patients with established DNR or DNI orders have already made decisions regarding their code status; therefore, including them would impede our ability to assess the intervention’s effect on code status decision-making. Auditory and visual impairments are not barriers to participation. The code status video includes subtitles, and patients have the option to have the research assistant administer the study survey verbally. All patients who meet the eligibility criteria will be offered enrollment within 48 hours whenever feasible.

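### ICU-free and ventilator-free days are zeroed only for death, so a dying patient discharged to hospice outscores an identical patient who dies in hospital

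*Protocol article*

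**What the plan says.** The Data Analysis Plan defines two of the free-day outcomes: "ICU-free days and ventilator-free days refer to the number of days during admission without intensive care or a ventilator". The next sentence gives the death rule: "In case of a death event, these variables are set to a value of 0". It sets no time window for the death and does not mention hospice.

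Procedures and Outcomes lists the wider group: "Hospital-free days, intensive care unit (ICU)–free days, ventilator-free days, discharge disposition, and rate of interventional procedures". These "will be collected from the electronic medical record". Hospital-free days is in this list, but the article does not define it, and the sentence before the death rule names only the ICU and ventilator outcomes. The one place that deals with deaths operationally concerns deaths in hospital: "For patients who die during admission, surrogate decision-makers will be contacted after discharge". No ascertainment of vital status after discharge is described.

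Hospice appears only in Study Population, as an exclusion at entry: "patients admitted while in hospice care". Discharge disposition is a separate secondary outcome and is not linked to the free-day scoring. Continuous outcomes are compared by the Wilcoxon rank-sum test.

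**The concern.** A death rule for free-day outcomes exists so that dying early is not rewarded as a short stay in intensive care. Here the rule responds to where a patient dies as well as to whether the patient dies. A death after transfer to hospice falls outside the admission and, on the data collection described, would not be seen.

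In many trials this would be noise shared equally by the arms. In this one the intervention concerns life-sustaining care. The sponsor's hypothesis is: "We hypothesize that our video aid will increase the rate of code status transitions, with more patients documenting their code status". The Discussion also cites an earlier single-center trial in which a video led more patients to choose DNR and DNI. Patients already in hospice are excluded, so a discharge to hospice is decided after enrolment and could be affected by the assigned arm. If it is, a change in the place of death would show up as a difference in ICU-free and ventilator-free days with no change in the use of intensive care or ventilation.

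**Working it through.** **Inputs from the article.** 15 patients per month for 18 months: 15 × 18 = 270, which reproduces the stated figure. With 1:1 allocation, 270 / 2 = 135 per arm. The test is the rank-sum test. The article states no significance level for it; two-sided 5% is assumed. It gives no figure for mortality, hospice discharge, length of stay or ICU use, so all of these are assumptions below.

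**Step 1: the rule applied to single patients.** Score = days in the admission − ICU days, set to 0 at death.

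| Patient | Score |
|---|---|
| 3 ICU days, dies in hospital on day 6 | 0 |
| 3 ICU days, to hospice on day 6 | 6 − 3 = 3 |
| 3 ICU days, survives, home on day 20 | 20 − 3 = 17 |
| No ICU, survives, home on day 4 | 4 − 0 = 4 |

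The first two have the same course and different scores. The hospice patient ranks above a death but need not rank high, because counting within the admission also rewards long stays.

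**Step 2: how many patients are involved.** If 10% are dying, that is 0.10 × 135 = 13.5 per arm. Raising the hospice share from 30% to 50% moves 0.20 × 13.5 = 2.7 patients off a score of 0.

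**Step 3: simulated rejection rate with no true effect.** Assumptions: lognormal stay (median 5 days, log SD 0.7), ICU share 0 to 0.7 of the stay, 10% dying in both arms, only in-hospital deaths scored 0.

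| Hospice share of dying patients, usual care v video | Rejection rate |
|---|---|
| 30% v 50% | 0.059 |
| 30% v 60% | 0.075 |
| 0% v 30% | 0.07 |
| 0% v 50% | 0.12 |
| 0% v 70% | 0.17 |

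The last three rows assume that usual care sends no dying patient to hospice.

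**Step 4: a second set of assumptions.** Stay median 7 days, half of patients with ICU days (median 3). P(video better) is the rank-sum effect; 0.5 means no difference.

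| Dying | Hospice share, usual care v video | P(video better) | Mean difference, days | Rejection rate |
|---|---|---|---|---|
| 10% | 20% v 20% | 0.500 | 0.00 | 0.052 |
| 10% | 20% v 40% | 0.509 | +0.14 | 0.058 |
| 10% | 20% v 60% | 0.518 | +0.29 | 0.078 |
| 20% | 20% v 60% | 0.536 | +0.59 | 0.166 |
| 10% | 40% v 20% | 0.491 | −0.14 | 0.064 |

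Equal shares give no bias. A lower share with the video reverses it.

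**Step 5: does a fixed window cure it?** With an assumed 28-day window, and the hospice share 20% v 40% or 60%, rejection ranges from 0.054 to 0.213 as the dying share goes from 5% to 20%. So a fixed window alone does not remove the problem.

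**Step 6: does scoring hospice discharge as 0 cure it?** In all the scenarios where it was tried (5 to 20% dying, hospice share 20% v 20 to 60%, both windows), P(video better) returns to about 0.50 and rejection to 0.042 to 0.054.

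**The case against.** A reader might infer that the rule biases the free-day outcomes in favour of the video. The documents do not support that. They give no hospice or mortality rates and state no expected effect on place of death. The direction depends on how the video changes the hospice share among dying patients, and a lower share reverses it. More DNR choices could also mean more deaths in hospital, which score 0 and count against the video: with 10% v 13% dying and equal hospice shares, P(video better) is 0.489. That scenario is a real difference in deaths rather than a scoring artefact, but it shows that the net direction cannot be read from the plan.

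A reader might also infer that all three free-day outcomes are inflated. Without a stated death rule for hospital-free days, moving a death to hospice cannot inflate that outcome by this route; there the article simply states no rule.

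The absence of vital-status follow-up is inferred from a condensed article. The full protocol or analysis plan may fix the window for death and the coding of hospice. That limits how firmly the point can be put, but the article does state a scoring rule, and the rule as stated has this consequence.

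Discharge disposition is compared in its own right, so a shift to hospice would be visible. That helps interpretation but does not correct the scores.

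Finally, scoring hospice discharge as 0 is not neutral. If the video moves an extra 5% of patients who are not dying to hospice, that version rejects in about 10% of trials, against the video. This objection stands and shapes the fix.

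**Conclusion.** The point holds, conditionally. As written, identical dying patients score differently according to where they die, and the intervention could plausibly change that. ICU-free and ventilator-free days can therefore be biased in either direction.

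The size is modest under ordinary assumptions. With 10% dying, 135 per arm and some hospice use in usual care (30%), rejection under no true effect is about 6 to 8% instead of 5% when the video share is 50 to 60%. About 17% is reached at 10% dying only if usual care has no hospice discharges and 70% shift, or otherwise with a dying share as high as 20%. None of these shares comes from the documents. The outcomes are secondary and the trial is a pilot whose primary outcome is unaffected, so this is minor.

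**What to change.** Before unblinding, prespecify an analysis of ICU-free and ventilator-free days in which in-hospital death and discharge to hospice are both scored 0. Report it beside the version in which only in-hospital death is scored 0. Apply the same death and hospice scoring to hospital-free days. Show in-hospital death and discharge to hospice by arm next to these outcomes. Claim a benefit only if the two versions agree.

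The cost is a few sentences of analysis text and one extra run per outcome; discharge disposition is already collected. The downside is that patients who go to hospice and live on are scored as deaths in the new version, and it counts against the video if the video moves patients who are not dying to hospice. That is why neither version should stand alone. Results says that 270 patients were enrolled as of April 2026 and that an abstract is planned by July 2026, so the change should be dated and made while the statistician is still blinded.
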